### Subjects of the study

The study cohort consists of a potential of over 12 000 Filipino children who were enrolled in a pneumococcal vaccine trial conducted in Bohol 2000 to 2004 between the ages of 6 weeks and 10 weeks. For the current study, these same subjects will be approximately between 16 years and 20 years of age.

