### Video-otoscopy data and diagnosis outcome classifications

Video-otoscopy analysis leading to disease classification takes into account all otoscopic abnormalities associated with acute OM, chronic non-suppurative OM and CSOM, as well as a non-OM diagnoses (eg, otitis externa) summarised in box 1. APPs document findings rather than immediately arrive at a diagnosis. Each video-otoscopic image is associated with a tympanogram type as to simulate pneumatic otoscopy, a proxy for the gold standard to diagnose middle-ear effusion.^14 15^ The gold standard for the presence of middle-ear fluid is detected only by myringotomy; however, this being impossible, the proxy methodology used here is based on the decisions made by the senior paediatric otolaryngologist with over 30 years of performing otologic procedures for complications from OM, including tympanoplasties and mastoidectomies. Given it would be impractical and impossible for the paediatric otolaryngologist to view thousands of video otoscopies, experienced otoscopists (APPs) have been trained and validated in identifying otoscopic abnormalities listed in box 1.

Box 1List of video-otoscopic finds depicting physical findings associated with otitis mediaRedness of tympanic membrane (TM).Opacification not due to scarring (dullness, thickened and webbing).Bubbles or air-fluid interfaces or fluid.Abnormal TM colour: white, yellow, amber or blue.Fullness or bulging of TM.Thinned out area of TM or healed perforation seen in 360°.Tympanosclerosis/scarring.Perforation small (<25% of TM).Perforation large (≥25% of TM).Retraction/retraction pocket/generally thinned out but not healed TM.Retraction/pocket bottom not seen.Otorrhoea not due to otitis externa (moisture).Granulation tissue or squamous debris.Otitis externa.

All video otoscopies that are deemed as poor quality by the APP are reviewed by the otolaryngologist of the study and would remained classified as poor quality or into one or more of the following TM findings.

Video-otoscopic findings for each ear will then merged with the four tympanometric output parameters and clinical medical history to arrive at discreet diagnoses (figure 1). Four broad diagnostic categories with definitions include normal, mild, moderate and severe ear disease. If two ears of a subject have disparate levels of middle-ear disease, the subject would be classified as having the more serious form of ear disease for the purpose of analysis.

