### Statistical analysis methodology

Demographic attributes and potential risk factors derived from the Parent Questionnaire will be analysed to determine which ones should be included in the multivariate analyses. A p value <0.15 will be used to select the ‘significant’ variables. ORs will be computed for the dichotomous categorical variables, using a Cochran’s Mantel-Haenszel statistic to compute the p value. Continuous variables and categorical variables with more than two categories will be analysed using Student’s t-test or Wilcoxon rank-sum test. A rank-sum test will be used when the assumptions required for the t-test are not met. When there are significant differences in ear disease classification between the vaccine and placebo group, then a multivariate logistic regression model will be derived to identify the vaccine efficacy for the 11-valent pneumococcal conjugate (11PCV) vaccine, and significant effects for the covariables.

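### Vaccine efficacy is tied to a logistic model and no risk-based measure is named; reported as 1 − OR, it would exceed 1 − RR unless the ear-disease endpoint is rare

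*Protocol article*

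**What the plan says.** All of the analysis text is in the protocol article under Statistical analysis methodology. It conditions the efficacy model on a significant difference between arms ("When there are significant differences in ear disease classification between the vaccine and placebo group") and then says that "a multivariate logistic regression model will be derived to identify the vaccine efficacy for the 11-valent pneumococcal conjugate (11PCV) vaccine". It gives no formula for efficacy.

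The only effect measure named is the odds ratio: "ORs will be computed for the dichotomous categorical variables, using a Cochran’s Mantel-Haenszel statistic to compute the p value". That sentence belongs to the screening of demographic and risk-factor variables, for which "A p value <0.15 will be used to select the ‘significant’ variables". No risk ratio or risk difference appears anywhere in the article.

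The outcome is defined under Video-otoscopy data and diagnosis outcome classifications: "Four broad diagnostic categories with definitions include normal, mild, moderate and severe ear disease". Where the two ears differ, "the subject would be classified as having the more serious form of ear disease for the purpose of analysis". The article gives no expected prevalence for any category and does not say whether the logistic model is binary, ordinal or multinomial.

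**The concern.** Vaccine efficacy is conventionally the relative risk reduction, 1 − RR. This study follows up a randomised cohort: "The study cohort consists of a potential of over 12 000 Filipino children who were enrolled in a pneumococcal vaccine trial". The denominators in each arm are known, so risks can be estimated directly and there is no design reason to settle for an odds ratio, as there would be in a case-control study. An analyst who follows the section as written fits a logistic model, reads off an odds ratio and reports 1 − OR.

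Two things are at stake.

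- **Size of the headline figure.** 1 − OR approximates 1 − RR only when the endpoint is rare. The article gives no basis for relying on that. The mild category alone covers acute otitis media, otitis media with effusion, healed perforation and myringosclerosis, and the worse-ear rule can only raise the subject-level proportion.
- **Stability of the headline figure.** The covariates are chosen from the data at p<0.15. An odds ratio conditional on covariates is non-collapsible: it changes when a covariate that predicts the outcome enters the model, even if that covariate is perfectly balanced between arms. The reported efficacy would then depend partly on the outcome of the screen.

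**Working it through.** **Inputs.** The article states no prevalence, effect size or efficacy figure, so there is nothing of its own to reproduce. The placebo prevalence p0 and the true efficacy VE below are assumptions, shown over a range.

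**Formulae.** With RR = 1 − VE and vaccine-arm prevalence p1 = RR × p0:

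- OR = [p1/(1 − p1)] / [p0/(1 − p0)] = RR × (1 − p0)/(1 − p1)
- therefore 1 − OR = VE/(1 − p1)

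If the vaccine protects, p1 lies between 0 and 1 and 1 − p1 is below 1. So 1 − OR always exceeds VE, and the excess grows with p1.

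**One case in full.** Take p0 = 0.30 and RR = 0.8. Then p1 = 0.24 and OR = (0.24/0.76)/(0.30/0.70) = 0.737, so 1 − OR = 26.3% against a true 20%. The short form agrees: 0.20/0.76 = 0.263.

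**Range: value of 1 − OR**

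| Assumed p0 | True VE 20% | True VE 30% | True VE 50% |
|---|---|---|---|
| 1% | 20.2% | 30.2% | 50.3% |
| 5% | 20.8% | 31.1% | 51.3% |
| 10% | 21.7% | 32.3% | 52.6% |
| 20% | 23.8% | 34.9% | 55.6% |
| 30% | 26.3% | 38.0% | 58.8% |

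The excess is about 1 point at 5% prevalence, 2 to 3 points at 10%, 4 to 6 points at 20% and 6 to 9 points at 30%.

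**Effect of the worse-ear rule.** Suppose 10% of ears are diseased (assumed). If the two ears of a subject always agree, 10% of subjects are classified as diseased. If the ears are independent, the figure is 1 − 0.9² = 19%. The subject-level prevalence, which is what matters for the table, can therefore be nearly twice the ear-level one.

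**What is not affected.** OR = 1 exactly when RR = 1, so the marginal comparison of no effect against some effect does not depend on the scale. The issue is the size of the efficacy reported, not a false positive finding.

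**Non-collapsibility.** This follows from the form of the odds ratio, but its size depends on how strongly the selected covariates predict ear disease. The article does not say, so no figure is attached.

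**How the categories enter the model.** Suppose proportional odds holds and the shares of normal, mild, moderate and severe are 60/20/15/5% (assumed). The information that a binary split keeps, relative to the ordinal model, is (1 − p³ − (1 − p)³)/(1 − Σ pᵢ³), where p is the proportion above the cut:

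- any disease: 93%
- moderate or worse: 62%
- severe only: 18%

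With shares of 90/6/3/1% the values are 99.7%, 42% and 11%. The choice of form therefore matters for precision as well as for meaning.

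**The case against.** The strongest reply is that the article never equates efficacy with 1 − OR. A logistic model can give a risk ratio by standardising its predicted risks, so the stated model is compatible with a correct efficacy estimate. The odds-ratio sentence concerns covariate screening and is not put forward as the vaccine effect measure. This stands as a limit on the claim: a reader might infer that the reported efficacy will certainly be inflated, and the text does not support that. It does not remove the point. The section fixes a model whose direct output is an odds ratio and gives no step that turns it into a risk-based figure.

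A second reply is that no prevalence is given and that the gap is 2 points or less at 10% prevalence or below for a true efficacy of 20%. That is correct. If the modelled endpoint were severe disease alone, and it proved rare, the difference would be trivial.

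A reader might also infer that the model is binary and discards the ordering, or that a cut will be chosen after seeing the data. The text supports neither. Logistic regression without further qualification does not exclude an ordinal or multinomial form, and the outcome coding may well be in a statistical analysis plan that is not shown. For the same reason the article's silence on a cut-point carries little weight by itself.

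**Conclusion.** The point holds in conditional form. The plan ties efficacy to a logistic model and names no risk-based measure, in a randomised cohort where risks can be estimated directly. If efficacy is reported as 1 − OR, it overstates 1 − RR whenever the vaccine protects: by under 1 point at 5% prevalence and by 6.3 points at 30%, for a true efficacy of 20%. The direction is certain given that reporting choice. The size rests on assumed prevalences and is material only if the endpoint is common, roughly above 10%. The dependence of the conditional odds ratio on the p<0.15 screen is a further reason to prefer a marginal risk ratio, but its size is unknown. The unstated handling of the four categories is a secondary request for clarification and not an error in the plan.

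**What to change.** In Statistical analysis methodology, define VE = 100 × (1 − RR) with a 95% CI. Estimate RR by modified Poisson or log-binomial regression with robust standard errors, or keep the logistic model and obtain RR by marginal standardisation of the predicted risks. Odds ratios can stay as a secondary display, labelled as such and not called efficacy.

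Before the unblinded analysis, also state how the four ordered categories enter the model: either an ordinal form or one named cut. No particular cut is prescribed here, since each binary split answers a different question and gives up a different amount of ordinal information.

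The cost is a few lines of text and code. The data are already to be exported as SAS files (Ethics section), no data collection changes, and the standardisation route keeps the planned model. The one downside is that the reported efficacy will look slightly less favourable than 1 − OR.

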## Discussion

The methodology discussed in this manuscript will be sed to analyse a potential cohort of 12 000 children previously enrolled in a pneumococcal vaccine trial in Bohol, Philippines, and will now be assessed 12–18 years later for the vaccine’s effects on otoscopic and audiologic endpoints. It is unique in several aspects: size of the cohort, clinical endpoints and complexity of data analysis.

The sample sizes of previously published randomised controlled pneumococcal conjugate vaccine trials have been clearly summarised by a recently published Cochrane Review.^19^ Our cohort of over 12 000 children to be assessed likely would be lowered since attrition might occur due to inability to locate the families due to relocation or immigration after 15–18 years, as well as parental refusal to participate. Regardless, the biggest pneumococcal vaccine trials were published by Black *et al* in 2000^20–22^ and Tregnaghi *et al*^23^ involving 37 868 and 24 000 subjects, respectively. Black’s study was conducted in the USA, and acute OM was the only ear-related outcome.^21^ The Tregnaghi *et al*’s study was done in Central and South American countries, but only 7214 children from Panama were included in the OM portion of the study.^23^ Prymula *et al* published an acute OM trial using an 11-valent pneumococcal vaccine conjugated to *Hemophilus influenzae*-derived protein D trial in 4968 subjects.^24^ This trial was conducted in the Czech Republic and Slovakia, and tympanocentesis and pneumococcal subtyping were done. A recent open label trial of maternal immunisation with a 23-valent polysaccharide pneumococcal vaccine in 227 indigenous mothers in the Northern Territory, Australia, showed no impact on OM-related infant outcomes at 7 months of age.^25^

The clinical outcomes for the randomised controlled trials have included the reduction of pneumococcal OM, recurrent OM, OM visits and tympanostomy tube insertions.^20–24 26^ None of these randomised controlled trials were focused on the long-term sequalae of OM in terms of changes in the TM as evaluated by otoscopy and changes in hearing as evaluated by audiometry. While prevention of disease is compelling for the use of the pneumococcal vaccine, preventing of long-term sequalae is just as important. Trials conducted in the indigenous populations in Australia that examined long-term sequelae occurred after licensure of pneumococcal vaccines in Australia and so followed before/after designs.^27–30^ Thus, our study will be among the largest randomised controlled pneumococcal vaccine trials for OM and the only one to study the long-term effects on OM sequelae 15–18 years after the initial trial.

The complexity of the methodology dealing with data lies at several levels. First, it requires the raw data collected by the local research team be uniform and robust. Despite a local research supervisor ensuring good quality data were recorded and uploaded, a certain degree of data scrubbing will be required on the US side. Tympanometric and audiologic data are codified based on published definitions of classifications. An algorithm has also been developed to derive OM diagnostic endpoints from all video-otoscopic images that was reliant on the raw images and tympanogram types. The overall construct of the methodology may serve as a platform for conducting large scale OM research in LMIC, particularly, if the objectives include garnering otoscopic and audiologic determinates and assessment of chronic and long-term OM complications.

## Ethics and dissemination

### Ethics

The ‘Do No Harm’ precept has been inculcated in the study. Despite the healthcare discrepancy that exists between the USA and Bohol, Philippines, accommodations have been made in the methodology to refer the research subjects to local healthcare professionals. The local field workers will be instructed to refer subjects to Bohol Hearing Centre for failed OAEs, tympanometry and/or screening audiometry and to the local otolaryngologist for ear pathology (inability to remove cerumen after instillation of mineral oil from a previous visit, otorrhoea and suspicion for cholesteatoma).

The study was approved by the Research Institute of Tropical Medicine, Alabang, Manila, Philippines, and the institutional review board (20 February 2016) and the Colorado Multiple Institutional Review Board of the University of Colorado School of Medicine, Aurora, Colorado, USA (16-0473).

Study data are collected and managed using REDCap electronic data capture tools hosted at University of Colorado. REDCap is a secure, web-based application designed to support data capture for research studies, providing: (1) an intuitive interface for validated data entry; (2) audit trails for tracking data manipulation and export procedures; (3) automated export procedures for seamless data downloads to common statistical packages and (4) procedures for importing data from external sources. Data are stored, managed and processed within the system. Data are exported as SAS (version 9.4) files to secure servers on the University of Colorado and Children’s Hospital Colorado systems, where data will be analysed.

### Dissemination

Research data are privately held. Research results will be made available to children and their caregivers with abnormal audiologic outcomes, the funders and other researchers. After publication, anonymised and curated data will be made available to researchers following guidelines of the Bill and Melinda Gates foundation. Data will be published in open access journals only.
